### Specific aims:

1. To determine the incidence of NVAF diagnosis in England from the year 2009 to 2019.
2. To determine the proportions of patients with NVAF and those with NVAF and cancer who were prescribed OACs, antiplatelet alone or no treatment.
3. To examine the temporal trends of prescribing different types of OACs (i.e. VKAs and NOACs), and assess the factors associated with not prescribing OACs including patient demographics, socioeconomic status, history of cancer and other comorbidities, stroke and bleeding risk.
4. To assess the effect of OACs prescribing vs. no OACs on the clinical outcomes (stroke, bleeding, and death) in a comparative cohort of NVAF patients eligible for anticoagulation after controlling for patients' comorbid conditions, frailty, age, and antiplatelets use.
5. To assess the rate of clinical outcomes (i.e. bleeding recurrence, stroke, and mortality) after MB events and how they relate to OACs resumption and the timing of restarting OACs after the MB event.
6. To explore the variability across patient groups regarding OACs resumption after MB events and whether patients have continued on the same OAC before the MB event, switched to another OACs or received lone antiplatelet therapy.
7. To assess and compare patients' risk for stroke and bleeding recurrence using HAS-BLED, CHA2DS2-VASC, HEMORR?HAGES and GARFIELD-AF risk assessment scores, at the time of the indexed major bleeding event.

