## Selection of comparison groups/controls

For the second phase of this study, we aim to compare the clinical outcomes of patients with NVAf prescribed OACs and who were not prescribed OACs. This will be done by including incident cases of NVAf identified from phase one cohort from 2009 to 2019 and further divide them into two groups; cases are patients treated with OACs within one year of NVAf diagnosis and controls are those who did not receive OACs for  $\geq 1$  year after NVAf diagnosis. Many confounders will be controlled for when evaluating the effect of treatment (OACs) on the clinical outcomes of interest (i.e. stroke, bleeding, or all-cause mortality). Potential confounders are likely to include patient age, sex, and presence of hypertension, diabetes, coronary artery disease, heart failure, kidney disease, liver disease, peripheral artery disease, fall risk, history of stroke or bleeding, malignancy, anaemia, alcohol abuse, antiplatelet use or non-steroidal anti-inflammatory drugs. At first, we aim to perform propensity score matching method using a multivariable logistic regression model that contains the confounders mentioned above to estimate patient's probability to receive OACs. Matching will operate by taking each case and finds the closest propensity score match among controls, within a predetermined caliper bandwidth. However, in case if the matching method failed to achieve balance among the two patient groups or caused substantial exclusion of individuals from the main cohort, then we will consider overlap propensity score weighting. By applying overlap propensity score weighting each patient's will be weight by the probability of that patient being assigned to the opposite treatment group.

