**Covariates:**

Covariates believed to potentially confound the relationship between anticoagulation therapy and the outcomes of interest were selected based on previously established associations. These includes age and sex (will be largely accounted for through the matched study design). Stroke risk assessment using CHA2DS2-VASc score and the GARFIELD-AF model, bleeding risk using HAS-BLED and HEMORR2HAGES scores, Charlson comorbidity index, eFI, and IMD.

Concomitant use of medications will also be described in the context of drugs that affect either stroke or bleeding, or commonly interacts with OACs. Such medications would include drug from therapeutic classes of aspirin and other antiplatelets, antihypertensive, statins, antiarrhythmics, diabetic drugs, anticonvulsants, non-steroidal anti-inflammatory drugs, corticosteroids, systemic azoles, HIV protease inhibitors and ciclosporin.

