2. Phase 2 – Comparative study: For comparison of demographic variables and comorbidities among OACs treated and not treated individuals, independent sample t tests will be used for numeric variables, while Chi squared  $\chi^2$  tests or Fisher exact tests will be used for categorical variables. To control for imbalances in patient characteristics between cohorts, we will calculate an exposure-specific propensity score as the predicted probability of receiving OACs conditional upon individuals baseline covariate (as described in section M) using logistic regression models. Then we will consider applying propensity score matching methods to match each OACs unexposed controls to up to 5 NVAF OACs exposed cases using a calliper of 0.2 standard deviation (SD) of the propensity score logit. After matching, Cox regression will be used to compute hazard ratios (HRs) of the outcomes of interest, comparing exposure to OACs versus no OACs. Initially crude HRs will be obtained, then stratified by type of OACs (i.e., VKAs and NOACs) and adjusted for age, and other important covariates described in section N. In this phase immortal time bias would occur due to the definition of exposure, where in the time from AF diagnosis till receipt of OACs those in the “OACs prescribed group” cannot have the outcome by design, otherwise they would have been classified as non OAC users. To avoid the problem of immortal time bias, we will consider using time-varying exposures, where in a survival analysis, the time period previous to the index date of OACs initiation is reclassified as nonuser for those in the “OACs prescribed group”.

3. Phase 3 – Major bleeding events cohort: At first, we will use descriptive statistics to present the overall characteristics of this cohort who have experienced major bleeding events while taking OACs. After that patients will be divided to 2 groups one for the patients who resumed anticoagulation after the index major bleeding event and the other for the group who remained OACs free and will compare the patient characteristics between the two groups using Chi squared  $\chi^2$  tests, Fisher's exact tests, and analysis of variance, as appropriate. Survival (time-to-event) models will be constructed to compare the time between the indexed major bleeding to the earliest event of stroke, bleeding, or all-cause mortality considering if patients were restarted on OACs or not. In Cox models we will control for age, time to OACs resumption, CHA2DS2-VASc

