### **Plan for addressing confounding**

In phase 2, we aim to conduct a comparison between NVAF patients who were exposed to OACs (cases) and patients who were not exposed to OACs (controls). We will calculate an exposure-specific propensity score as the predicted probability of receiving OACs conditional upon the effect of potential confounders (described in section M). Then we will use a propensity score matching method to achieve similarity of measured confounders across cases and control groups. When estimating HRs using Cox regression models for the outcomes of interest among patient groups, we will also adjust for age, sex, IMD, stroke risk, bleeding risk, frailty, Charlson comorbidity index, and prescription of antiplatelets.

In phase 3, when looking at the predictors of restarting OACs after the indexed bleeding events we will take in account many confounders that could influence this decision, this will be done by using a multinomial logistic regression to adjust for the covariates described in section N. These covariates will also be considered when conducting survival analysis to compare the time between the indexed major bleeding to the earliest event of stroke, bleeding, or death among patients who restarted OACs and those who did not. Also, when evaluating the outcomes of restarting OACs we will consider the timing of restarting anticoagulation after bleeding, and stratify patients based on different time periods of OACs reinitiating.

In both phase 2 and 3, an additional analysis will be considered to assess the robustness of results to unmeasured confounding using the E-value methodology. This estimates what the relative risk would have to be for any unmeasured confounder to overcome the observed association of OACs prescribing with the clinical outcomes of stroke, bleeding, or mortality.

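### The Phase 2 propensity-score list omits frailty, deprivation and the Charlson index, which the protocol itself names as confounders, so their control rests on the Cox model alone

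*Protocol*

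**What the plan says.** The section on selection of comparison groups/controls gives the confounder list for Phase 2. It opens "Potential confounders are likely to include patient age, sex, and presence of hypertension", continues through individual cardiac, vascular, renal and hepatic conditions, and ends "fall risk, history of stroke or bleeding, malignancy, anaemia, alcohol abuse, antiplatelet use or non-steroidal anti-inflammatory drugs". Matching is then to be done "using a multivariable logistic regression model that contains the confounders mentioned above to estimate patient's probability to receive OACs". If matching fails to balance the groups or discards too many patients, "then we will consider overlap propensity score weighting"; no separate covariate set is given for that fallback.

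The Phase 2 part of the data/statistical analysis section defines the score "conditional upon individuals baseline covariate (as described in section M) using logistic regression models". The plan for addressing confounding points to section M as well. The headings in the text carry no letters, but by content section M is the comparison-group section and section N is the section on exposures, outcomes and covariates.

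The Phase 2 covariates paragraph (section N) presents its variables as ones believed to confound the treatment-outcome relation. It ends with "Charlson comorbidity index, eFI, and IMD". Aim 4 undertakes to control for "comorbid conditions, frailty, age, and antiplatelets use".

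For the outcome models, the confounding plan states that "we will also adjust for age, sex, IMD, stroke risk, bleeding risk, frailty", and goes on to the Charlson index and antiplatelet prescription. The analysis section reports crude hazard ratios first, and then hazard ratios adjusted for age and the section N covariates.

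**The concern.** One comparison has two confounder lists, and the design stage is tied to the one that lacks three of the named confounders. A propensity score balances what is in it. A variable left out is balanced only as far as it is correlated with the variables included. The protocol gives the purpose of matching as similarity on measured confounders. eFI, IMD and the Charlson index are measured, and the protocol itself regards them as confounders.

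If frailer patients are less often anticoagulated and have worse outcomes, the crude matched or weighted hazard ratio will look too favourable to anticoagulation. The adjusted hazard ratio would then depend on how frailty and deprivation enter the Cox model, without the protection that a propensity design is meant to add. The planned E-value analysis does not cover this, because it addresses unmeasured confounding.

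**Working it through.** **Step 1: compare the lists.** The plan states no figure on this point, so the main check is textual.

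| Variable | Propensity list (section M) | Phase 2 covariates (section N) | Cox adjustment (confounding plan) |
|---|---|---|---|
| Age, sex | yes | yes | yes |
| Frailty (eFI) | no; fall risk only | yes | yes |
| IMD | no | yes | yes |
| Charlson index | no; many single conditions | yes | yes |

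The gap is confined to the design stage. Age, fall risk and the single conditions partly stand in for frailty and the Charlson index. Nothing in the list evidently stands in for IMD.

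**Step 2: size before outcome-model adjustment.** The documents give neither the frailty prevalence after matching nor its effect on outcome, so all inputs are assumed. Let p0 and p1 be the proportions frail among unexposed and exposed patients after matching, h the frailty hazard ratio, and 1.0 the true treatment hazard ratio. Approximately:

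apparent HR = (1 + p1(h − 1)) / (1 + p0(h − 1))

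- p0 = 0.25, p1 = 0.20, h = 2: 1.20/1.25 = 0.96
- p0 = 0.25, p1 = 0.15, h = 2: 1.15/1.25 = 0.92
- p0 = 0.30, p1 = 0.15, h = 2.5: 1.225/1.45 = 0.845
- p0 = 0.30, p1 = 0.10, h = 2.5: 1.15/1.45 = 0.79

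**Step 3: does the planned Cox adjustment repair it?** This was checked with an illustrative simulation, with one run of 40,000 patients per scenario. Frailty was more common at higher age. Treatment depended on age and frailty. The true treatment hazard ratio was 0.60. The propensity score contained age only, and overlap weights were applied.

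| Frailty odds ratio for non-prescription | Frailty hazard ratio | Frailty standardised difference after weighting (absolute) | Weighted HR, unadjusted | HR with age and frailty in the Cox model |
|---|---|---|---|---|
| 1.5 | 1.5 | 0.190 | 0.578 | 0.598 |
| 1.5 | 2.0 | 0.190 | 0.551 | 0.585 |
| 2.5 | 1.5 | 0.407 | 0.576 | 0.620 |
| 2.5 | 2.0 | 0.423 | 0.530 | 0.608 |

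Age was balanced in every scenario (standardised difference 0.000), but frailty was not. The unadjusted hazard ratio was 0.53 to 0.58, too favourable to treatment. With frailty in the Cox model it was 0.585 to 0.620, close to 0.60.

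Two limits apply. These are single runs, so the spread includes simulation error. The Cox model was also given frailty in exactly the form that generated the data, so the result shows what a correctly specified model achieves and does not test a misspecified one.

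**The case against.** The strongest reply is that the confounders are controlled where it counts. The Cox models adjust for frailty, IMD and the Charlson index. Aim 4 promises control for frailty, not balance through the score, and Cox adjustment meets it. Matching first and adjusting for further covariates afterwards is a legitimate two-layer plan. The hazard ratios most exposed to bias are the ones that the protocol itself calls crude. All of this stands. A reader who sees only the propensity list might infer that frailty is left uncontrolled; the confounding plan contradicts that.

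The list is also worded as what confounders are likely to include, so it is not strictly closed. The section on planned use of linked data says that IMD will be a covariate in the regression models of all three phases, which could be read to cover the propensity model. These points soften the inconsistency but do not settle it: the propensity model is said to contain the listed variables, and both later sections refer back to that list.

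Two further inferences are tempting and unsupported. The first is that frailty is a main driver of non-prescription. The study background instead attributes under-prescribing in elderly patients mainly to overestimated bleeding risk. The second is that the balance check could not reveal the gap. The protocol does not restrict that check to the variables in the score, and all three could be tabulated.

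Finally, the partial proxies in the score may make the residual gap smaller than the larger gaps assumed above. That is fair, and it is why the 0.96 case is shown.

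**Conclusion.** The point holds as an inconsistency between the two covariate lists, with limited consequences. Three variables that the protocol regards as confounders are missing from the model meant to balance measured confounders, and the overlap-weighting fallback inherits the omission. The planned Cox adjustment largely protects the adjusted hazard ratio if it is correctly specified. What remains is possible imbalance on these variables, crude matched or weighted hazard ratios that may be confounded, and control of frailty and deprivation that rests on one model.

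The figures of 0.79 to 0.96 for a true 1.0, and 0.53 to 0.58 for a true 0.60, rest on assumed frailty prevalences and effects and apply only before outcome-model adjustment. They do not show that the adjusted Phase 2 result would be biased. No size was estimated for IMD or the Charlson index. This is a robustness improvement at almost no cost, not a flaw that invalidates the comparison.

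**What to change.** Align the propensity list in the comparison-group section with the Phase 2 covariates section:

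- Add eFI, IMD quintile and the Charlson index, all measured at NVAF diagnosis, to the propensity model, and state that the same set is used for overlap weighting.
- Include the three variables in the balance assessment that decides whether to move from matching to overlap weighting, and report their balance.
- Keep the Cox adjustment in the confounding plan as a second layer.

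All three are already planned covariates in Phases 1 and 2, so no new data or derivations are needed. The cost is a wording change and three more entries in the balance table.

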## Exposures, outcomes and covariates

### 1. Phase 1 – NVAf Cohort

**Exposures:** At least one diagnostic code of AF which will be defined specifically as a diagnosis of non-valvular AF (as listed in Appendix 1), up to 30th June 2019. Primary care patient clinical, and referral records will be used to identify exposures.

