## 2. Phase 2 - Comparative study

**Exposures:** In this cohort, prescriptions for OAC will determine patient’s exposure status. NVAf patients identified from phase one and who have received a continuous prescription of either VKAs or NOACs within one year of NVAf diagnosis will be in the OACs “exposed group”. While “OACs unexposed” patients are individuals in phase one who haven’t received a prescription for anticoagulation therapy and remained OACs free for  $\geq 1$  year from NVAf diagnosis.

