### Outcomes:

The primary outcome is the composite of ischaemic stroke and other thromboembolic events, or the occurrence of MB events defined according to the ISTH criteria (described in detail in Section D). Secondary outcomes will include CRNMB events that did not satisfy the ISTH criteria and led to hospitalization, medical or surgical treatment, or led to discontinuation of OACs. All outcomes will be identified over the course of follow-up through the identification of corresponding Read codes in patients’ records. For bleeding events since CPRD does not state the number of transfused blood units, any need for blood transfusion along with a Read code for bleeding will be classified as a MB event. Stroke or bleeding events will be identified through Read codes in patients primary care records and through linkage to inpatient HES ICD-10 codes in case of hospitalization secondary to stroke or bleeding. ONS mortality data will be used to ascertain specific causes of death (i.e. bleeding related, cardiovascular, or all-cause death) according

ICD-10 codes. All codes relevant to these outcomes are listed in Appendix 3.

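### Phase 2 does not require an outcome event to be new, so the stroke that revealed AF can be counted as an outcome

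*Protocol*

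**What the plan says.** - **Source of AF.** Under Exposures, outcomes and covariates, Phase 1: "Primary care patient clinical, and referral records will be used to identify exposures". HES is not named there.
- **Source of outcomes.** Under Phase 2, Outcomes: "Stroke or bleeding events will be identified through Read codes in patients primary care records and through linkage to inpatient HES ICD-10 codes". The window is given only as "All outcomes will be identified over the course of follow-up". The protocol states no start date, no gap after diagnosis, and no rule for linking GP and HES records of one event.
- **Earlier stroke.** Selection of comparison groups/controls lists "history of stroke or bleeding" among the confounders. The Phase 1 covariates give prior stroke two points in CHA2DS2-VASc. Neither makes it an exclusion.
- **Code lists.** The items of that score are drawn from Appendices 3 and 4. The Phase 2 outcome codes are in Appendix 3.
- **Exposure.** Exposed patients are those who "received a continuous prescription of either VKAs or NOACs within one year of NVAf diagnosis". Data/statistical analysis, item 2, describes immortal time as arising "where in the time from AF diagnosis till receipt of OACs". It then says "we will consider using time-varying exposures", under which "the time period previous to the index date of OACs initiation is reclassified as nonuser".

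**The concern.** AF is often found because a patient is admitted with a stroke. The practice then codes AF and the stroke from the discharge letter, or codes the stroke again at a later contact. If the stroke code carries the AF date or a later one, it meets the Phase 2 outcome definition even though the event came before, or with, the start of follow-up. One stroke can then be both a baseline covariate and a primary outcome. The same gap applies to thromboembolism and bleeding.

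This affects the study's central comparison, anticoagulant against none. Matching on stroke history does not cure it, because the error is in the outcome. The planned E-value addresses unmeasured confounding, not outcomes that are not new.

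**Working it through.** **1. How the text treats each record of the stroke that revealed AF**

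| Record | Date relative to GP AF code | Treatment as written |
|---|---|---|
| HES admission for the stroke | before | history, outside follow-up |
| GP stroke code | same day | no rule |
| GP stroke code | later | outcome |
| Later HES episode of the same stroke | later | outcome |

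The problem lies in the last three rows. The first row is already handled, so dating AF from GP data alone does not create the problem.

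**2. Which group carries the event**

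- *Time-varying exposure.* Time from AF diagnosis to first anticoagulant is non-user time. A re-coded stroke close to diagnosis falls there, including in patients who later start treatment. The bias favours anticoagulants.
- *Fixed groups.* Anyone treated within one year is exposed, so a re-coded stroke in such a patient counts against anticoagulants, while one in a never-treated patient counts against no treatment. The analysis section's own remark, that patients with an outcome before treatment would have been classed as non-users, points the other way. The net direction is uncertain.

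**3. Illustration of size**

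The protocol gives no figure on this point. The usable inputs are the yearly stroke risks in Sample size considerations: 8% without anticoagulants and 2.8% with warfarin. Their ratio is 0.028 / 0.08 = 0.35; the inverse, 2.86, corresponds to the stated relative risk of 2.8.

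Let d be the assumed share of patients whose earlier stroke is counted on non-user time.

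Apparent untreated risk = d + (1 − d) × 0.08; apparent ratio = 0.028 / that risk.

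| d (assumed) | Apparent untreated risk | Apparent ratio |
|---|---|---|
| 0 | 8.0% | 0.35 |
| 1% | 0.010 + 0.0792 = 8.9% | 0.31 |
| 2.5% | 0.025 + 0.0780 = 10.3% | 0.27 |
| 5% | 0.050 + 0.0760 = 12.6% | 0.22 |

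**4. Dependence on the model**

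A person-time version uses the 14,000 untreated patients in Feasibility counts. It assumes full 5:1 matching (70,000 treated), one year of follow-up, 30 days from AF to first anticoagulant, and 1% of all 84,000 patients affected (840 events).

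- Non-user person-years: 14,000 + 70,000 × 30/365 = 19,753.
- True non-user strokes: 0.08 × 19,753 = 1,580.
- Observed non-user rate: (1,580 + 840) / 19,753 = 0.1225.
- Observed ratio: 0.028 / 0.1225 = 0.23, against 0.31 in the simpler calculation.
- With no true effect (5% a year in both groups): (988 + 840) / 19,753 = 0.0925, so the ratio is 0.05 / 0.0925 = 0.54 instead of 1.

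With lags of 14 to 90 days and shares of 0.5% to 5%, a true 0.35 appears as anything from 0.30 to 0.08. The answer depends almost wholly on assumed inputs.

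**The case against.** A reader might infer three stronger things, and the document supports none of them.

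- **That GP-only dating of AF is the cause, and HES dating the cure.** A HES stroke before the GP AF code is already history. Moving the index date back to the admission could create same-day ties and place every post-discharge GP stroke code after the index date. It would also shift Phase 1 incidence dates, risk scores and one-year exposure windows. The protocol uses linkage-eligible patients only for particular phases, so HES dating may not be available throughout.
- **That the bias must favour anticoagulants.** That holds under time-varying exposure, which the protocol will only consider.
- **That the size is known.** The 1% to 5% is assumed, and the rates are for stroke alone, whereas the Phase 2 primary outcome also includes major bleeding.

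It can also be said that outcomes found during follow-up and scores measured at the index date already separate history from outcome in principle; that the appendices are not visible, so the presence of review codes cannot be asserted; and that event-linking rules often sit in an analysis plan. The first point covers events dated before the index date, but not later codes for an old event. The second is right, and the point does not depend on review codes. On the third, the protocol itself sets the sources and some case rules, for example transfusion plus a bleeding code as major bleeding. As written, those definitions admit the old stroke. An unseen plan may add a rule, but the protocol text would still need to agree with it.

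**Conclusion.** The point holds as a gap in the Phase 2 outcome definition: nothing shown requires an outcome event to be new, so the stroke that revealed AF can be counted when a record of it is dated on or after the AF date. The result is biased towards anticoagulants if the time-varying analysis is used, and in an uncertain direction under the fixed groups. That follow-up starts at AF diagnosis is inferred from the immortal-time text, since the outcome section does not say so.

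The size cannot be derived. The shift from 0.35 to between 0.31 and 0.22 is an illustration resting on an assumed 1% to 5%, on all affected events falling on non-user time, and on stroke-only rates. It shows that a small share would matter, not how large the bias is. The change should be made before outcome data are extracted.

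**What to change.** In the Phase 2 outcome definition:

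1. Treat any stroke, thromboembolism or bleed dated on or before the index date as history only.
2. After the index date, count an event only if it is a new HES admission for that event, with linked transfers and continuing episodes treated as one admission, or a GP code with no same-type GP or HES record in a stated preceding window. A window of 90 days is one example; vary it in a sensitivity analysis.
3. Do not count any history or review codes as outcomes.

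Dating AF at the earlier of the GP and HES codes is optional, as a sensitivity analysis in linked Phase 2 patients. It is not the core fix.

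The cost is wording and extraction logic on linkages already requested. The downside is that a few true early repeat events recorded only by the GP would be missed.
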